**0. Type of application**

First trial for a new indication.

**2. Title of the clinical trial**

# Pilot study of the effect of a CCR5 coreceptor antagonist on the latency and reservoir of HIV-1 in patients taking highly active antiretroviral therapy

**3. Protocol code**

ERRADVIH-01

EudraCT No. 2007-003995-21

**5. Centers where the study is to be carried out**

Servicio de Enfermedades Infecciosas, Hospital Ramón y Cajal.

**6. Institutional Review Board to evaluate the trial**

IRB of Hospital Hospital Ramón y Cajal.

**8. Experimental drug and control drug**

Study drug:

Maraviroc (INN), 150 and 300-mg tablets, developed and supplied by Pfizer, S.A. One dose of 150-600 mg will be administered every 12 hours according to technical data and the previous antiretroviral treatment of each patient.

Control drug: Not applicable.

**9. Phase of trial**

Phase II clinical trial.

**10. Primary objective**

To evaluate the influence of treatment with a CCR5 coreceptor antagonist (Maraviroc) on the reservoir of HIV-1 in patients taking highly active antiretroviral therapy.

**11. Design**

Phase II Open Clinical Trial carried out in one centre

**12. Study pathology or disorder**

Infection by the human immunodeficiency virus (HIV)

**13. Primary endpoint**

Size of the latent reservoir measured as the number of resting CD4+ T lymphocytes containing a competent replicating virus.

**14. Study population and total number of patients**

Adult patients with HIV infection and a viral load that has been suppressed for a long period (less than 50 copies/mL for at least 2 years) while on antiretroviral therapy. The study will include 10 patients that maintain the habitual antiretroviral therapy combined with maraviroc.

**15. Duration of treatment**

12 months

**16. Calendar and expected end date**

After approval by the IRB and other regulatory bodies:

- Enrollment of patients: 6 months
- Duration of therapy and follow-up: 12 months

The study is expected to finish 18 months after approval.

# GENERAL INFORMATION

## **Identification of the trial**

**Protocol code:** ERRADVIH-01

**EudraCT no.:** 2007-003995-21

# Title: Pilot study of the effect of a CCR5 coreceptor antagonist on the latency and reservoir of HIV-1 in patients taking highly active antiretroviral therapy

## **Type of clinical trial**

Phase II open clinical trial carried out in one center

## **Study products**

**Study drug:**

Maraviroc (INN), 150 and 300-mg tablets, developed and supplied by Pfizer, S.A. One dose of 150-600 mg will be administered every 12 hours according to technical data and the previous antiretroviral treatment of each patient.

**Control drug:** Not applicable.

## **Study center**

Hospital Ramón y Cajal

## **Expected duration of the trial**

18 months

# RATIONALE AND OBJECTIVES

## **Origin of the project**

HIV-1 infection and AIDS are still among the most serious threats to mankind. To date, the AIDS pandemic has killed more than 28 million people and infected 42 million throughout the world. Despite prevention campaigns and new treatments, it is estimated that there will be 45 million new HIV-1 infections by the end of 2010.

Scientific advances in virology and molecular biology have made it possible to identify each step of the viral cycle and this has enabled us to develop combined drug therapy that acts on the different steps of the cycle (ie, reverse transcriptase and protease). This therapy, known as highly active antiretroviral therapy (HAART), has made it possible in approximately 70% of all treated patients to reduce the number of virus copies in plasma to levels that are undetectable using the most common molecular techniques (detection threshold: 50 copies of RNA/mL), thus reducing the morbidity and mortality associated with HIV infection and AIDS. Similarly, the development of increasingly potent antiretroviral drugs with more comfortable dosing schedules means that all antiretroviral treatment guidelines agree on recommending that the objective to be reached with HAART is an undetectable viral load in all patients, even in those whose treatment has already failed. Therefore, in developed countries, we now have drugs to maintain the level of viral replication below 50 copies of RNA/mL.

Patients who respond well to HAART enter a stable clinical phase with very low viremia and recovery of the immune system. Today, many HIV-1-infected patients remain clinically stable for several years with HAART. Nevertheless, this type of therapy does not act on the latent form of the virus, which is found in those cells that make up the so-called viral reservoir. Thus, when this therapy is interrupted in patients with an undetectable viral load, there is a rapid rebound in viremia and progression to AIDS, with the result that patients are obliged to maintain HAART indefinitely (Finzi et al., 1999). This treatment is very aggressive and has severe side effects that often lower the patient’s quality of life. Furthermore, it is very expensive.

Recently developed ultrasensitive techniques capable of detecting levels as low as 1 copy of RNA/mL have shown that although viral replication supposedly suppressed by HAART continues, it is still possible to detect viral replication below 50 copies. We do not know the origin of this replication, although there are 2 potential sources: release of viral particles from reservoirs where the virus was “latent” (reservoirs and sanctuaries), and residual replication that cannot be suppressed with available antiretroviral drugs (Siliciano JD, 2006). In theory, more potent antiretroviral therapy could be efficacious against residual replication, although it would continue to be inefficacious against a virus that is latently integrated in viral reservoirs.

Therefore, owing to the lack of effective vaccines, the development of new therapies that act on the viral reservoir is currently one of the most important challenges in the fight against AIDS.

**In vivo viral latency**

During primary infection, HIV disseminates to lymphoid and nonlymphoid tissue. It has been shown that, despite HAART in patients with no detectable viremia, HIV can be detected in cells of the CNS, genitourinary system, and lymphoid tissue associated with intestinal mucosa (Fierer DS, 2006; Galván SR, 2006; Blankson JN, 2006). One of the reasons why the virus is not eliminated from these sanctuaries could be the fact that antiretroviral drugs find it difficult to gain access (especially in the CNS) and also that infected cells escape the vigilance of the immune system. There is very little information on whether these reservoirs (sanctuaries) act as a source of residual replication in the presence of HAART or as pure reservoirs of latently integrated viruses.

From a clinical viewpoint, a small number of CD4+ memory cells are currently believed to represent the most important reservoir of HIV (Finzi et al., 1999). This reservoir has been calculated to be approximately 106 cells, in other words, there is 1 cell reservoir for every 106 resting CD4+ cells (Chun et al., 1997).

The therapeutic approach to viral latency requires viral reactivation in the presence of HAART (Yang QE, 2004), a selective attack with immunotoxins against latently infected cells (Brooks, et al., 2003), and intensification of HAART (Ramratnam et al., 2004), although this is far from being a reality in the treatment of AIDS.

Productive HIV infection in CD4+ cells is a complicated biological process that occurs when different cellular and viral events take place simultaneously. After the virus enters the host cell, the viral replication cycle will depend on cell activation status. Thus, infection of resting CD4+ cells gives way to incomplete viral reverse transcription, which represents a short period of viral latency with preintegrated HIV (Bukrinsky et al, 1991; Korin and Zack, 1998). If the cells are stimulated during the first 3 days after infection, the process of reverse transcription is completed and the viral cycle progresses to a productive infection (Namikawa et al., 1990). However, some of these infected cells return to a quiescent state (postintegration latency in memory cells) and represent one of the greatest problems for eradicating the virus from the body (Han et al., 2007).

This reservoir is established during the earlier phases of the infection and is obviously favored by the high viremia and hyperactivation of the immune system. The biology of the memory cells themselves means that the half-life of this reservoir has been calculated to be 44.2 months; therefore, the complete eradication of the reservoir would need 73.4 years of HAART (Siliciano et al., 2003). Nevertheless, these calculations depend on the real nature of the viral reservoir. In all patients studied with optimally performing HAART (the viral load in plasma is maintained below 50 copies of RNA/mL for several years), low levels of viremia may be due to residual replication, release of viruses from the reservoir, or a combination of both. Whereas some authors defend the idea that the reactivated viruses from the reservoir do not contribute to its subsequent maintenance (Siliciano, 2006) and, therefore, intensification of HAART would not be effective at reducing the size of the reservoir, other authors have shown that there is a clear communication between residual replication and maintenance of the reservoir, as exchange of viral particles between both compartments has been reported (Chun et al., 2005). According to these authors, the inclusion of integrase inhibitors and CCR5 coreceptor inhibitors would be expected to have a considerable influence on the dynamics and maintenance of this viral reservoir. This is one of the main objectives of this project.

**In vitro viral latency**

The main problem when attempting to understand the molecular mechanisms in viral latency is the lack of suitable models, as the frequency of latent infection in HIV-1-infected individuals is extremely low and neither the homogeneity of this reservoir nor the differences between individuals are well known. Nevertheless, groups including those of Jerome A. Zack and Eric Verdin have established 2 models that may indeed play an important role in the study of viral latency. The first is based on the SCID-hu murine model where liver and thymus tissue from human fetuses are implanted in SCID mice. These reconstitute an immune system that can be infected by HIV. In this model, some thymocytes contain inactive transcriptionally integrated virus that can replicate after cellular activation (Brooks et al., 2001). The second model uses a retroviral vector based on HIV to infect lymphoid cell lines by generating a cell clone library where expression of GFP correlates with the HIV-1 integration site (Jordan et al. 2003). This strategy has enabled us to establish a series of clones that express the virus latently and that can be reactivated using cell activation with TNFα or PMA (Jordan et al. 2003). These “latent” clones have been used in the study of the molecular mechanisms of viral latency (Williams et al., 2006) and for the study of the mechanisms of action of pharmacological compounds that act on viral latency (Williams et al., 2004, Márquez et al., 2007; Dauobi et al., 2007).

The use of lines latently infected with HIV has given way to new concepts about the molecular mechanisms that regulate viral latency. These concepts enrich our knowledge of this state of latency and are not completely exclusive—other models have been put forward. Thus, we have seen that p50, the subunit of NF-κB, interacts with HDAC1 and this complex favors maintenance of viral latency via changes in the structure of chromatin that prevent the recruitment of RNA pol II (Williams et al., 2006). It must be stressed that in primary resting lymphocytes there is an accumulation of p50 in the nucleus that acts by repressing genes that depend on NF-κB. When the cell is activated by the TCR or cytokines, the homodimers of p50 are substituted by heterodimers p50/p65 of NF-κB, thus producing the transcription of genes that depend on NF-κB, including HIV-1 LTR. In addition to p50, other factors such as YY1/LSF or even AP-4 can probably also recruit HDCA1 by favoring viral latency (He and Margolis, 2002; Imai and Okamoto, 2006). The absence of RNA pol II binding to latent LTR prevents the initiation of transcription, even in the presence of Tat (Williams et al., 2006). Therefore, viral latency may be governed by Tat levels and, especially, by the chromatin acetylation/deacetylation balance. This concept may explain the fact that trichostatin A (TSA) sensitizes latent LTR to the action of Tat. In other words, TSA favors the initiation of transcription required for the action of Tat on elongation (Williams et al., 2006).

It is worthy of note that these basic concepts can be extrapolated to the clinical management of viral latency. A recent study published by the RJ Bosch group has shown that valproic acid (VPA), an anti-epilepsy agent with HDAC-inhibiting action, can be effective for the treatment of viral latency in HIV-infected patients (Lehrman et al., 2005). This observation, although very limited by the number of patients involved, had been confirmed previously in vitro and therefore represents an important line of research in the treatment of viral latency. However, another, more recent study was not able to confirm the effect of VPA on the reduction in the size of the viral reservoir (Siliciano et al., 2007), Furthermore, the reduction in the reservoir observed by the Margolis group (Lehrman et al., 2005) was quite limited. Given that the reservoir must be almost 100% eradicated, it seems obvious that VPA alone could never be an option for eradicating the virus, although it could boost the effect of some pharmacological reactivators.

**Treatment of viral latency**

To date, clinical work on eradicating the viral reservoir has been based on the so-called immune activation therapy (IAT). This therapy has a double objective: first, it aims to induce viral replication and, thus, the new viruses produced would be sensitive to HAART; and second, the expression of viral antigens in the setting of MHC class-I would turn these cells into target cells of the immune response that would collaborate in the elimination of the viral reservoir. Several research groups have tried using the anti-CD3 monoclonal antibody OKT3 alone or in combination with IL-2, although without success. Another important candidate for the treatment of viral latency would be IL-7. This cytokine has been reported to be a potent reactivator of some HIV-1 subtypes in isolated T cells in patients taking HAART (Wang et al., 2005) and in the murine SCID-hu model of viral latency (Scripture-Adams et al., 2002). The latter group reported that combination therapy with IL-7 and immunotoxins induces depletion of the latently infected T cells (Brooks, et al., 2003).

An alternative to immunotherapy would involve drugs capable of reactivating viral latency, such as HDAC inhibitors (VPA) and some types of phorbol and diacylglycerol analogs (DAG), which do not present tumor-promoting activity. One of these derivatives is Prostratin (12-deoxyphorbol-13-acetate), which has been proposed for phase I clinical trials (AIDS Research Alliance, USA) (Hezareh, M. 2005). Prostratin induces reactivation of viral latency in vivo and in vitro (Brooks et al., 2001) by preferential activation of the PKCα and θ pathway and, as a consequence of this, the canonical activation pathway of transcription factor NF-κB is activated (Trushin et al., 2005). In addition to activating the NF-κB pathway, these deoxyphorbols induce endocytosis of HIV receptors (CD4 and CXCR4), which would mean that, as well as reactivation of the latent virus (susceptibility to HAART), reinfection of new CD4 cells would be avoided during the period of treatment with this type of compound (Hezareh, M. 2005). Despite the published data on the toxicity of prostratin and other deoxy-esters of phorbol in vivo, some authors maintain that, in order to reactivate viral latency, relatively high doses of this compound are necessary, which could be a serious limitation for development of the drug (Williams et al., 2004). Therefore, it would be interesting to study other more potent activators of viral latency, either alone or in combination with inhibitors of HDACs and/or IL-7, as proposed in some of the objectives of this study.

# Rationale

The presence of a pool of cells latently infected by HIV-1 in patients taking HAART and with a viral load below 50 copies/mL is the main limitation to eradication of the virus from the body. This viral reservoir prevents antiretroviral therapy from being interrupted; therefore, patients are obliged to continue with treatment for a period calculated to be greater than 60 years.

Despite the important advances in knowledge of the biology of this reservoir, we still have no real knowledge about its dynamics. The opportunity to carry out a clinical trial for the first time with CCR5 coreceptor antagonists is exceptional, since the results could provide important information on the nature of this reservoir.

If maintenance of the reservoir is a dynamic process, inclusion of CCR5 inhibitors is expected to lead to a reduction in the size of this reservoir. This effect could be critical when including IAT (viral reactivation), since, in theory, it would be necessary to act on a smaller reservoir. Current consensus is that it would be necessary to act on almost 100% of the viral reservoir (approximately 106 cells).

The study has also been designed to enable us to understand the biochemical and molecular mechanisms by which certain drugs can induce viral reactivation in vitro as a previous step to a clinical trial aimed at reactivating viral latency and eradicating HIV-1 from the body.

## **Primary objective**

To evaluate, by means of a controlled clinical trial, the effect of therapy with a CCR5 coreceptor antagonist (Maraviroc) on the cell reservoir of HIV-1 on patients taking HAART.

## **Secondary objectives**

1. To quantify in vitro the viral reservoir of these patients throughout the study.

2. To study in vitro the residual viremia using an ultrasensitive PCR assay (Single Copy Assay) and the Episomal 2-LTRs DNA circles detection.

3. To study the immune activation markers as indirect markers of residual viremia

# TYPE OF TRIAL AND DESIGN

## **Clinical trial phase**

Phase II

## **Randomization process**

Not applicable

## **Type of control and design**

Not applicable

## **Blinding techniques**

Not applicable

## **Enrollment, washout, and follow-up**

The enrollment period will be 6 months. There will be no washout period. The initial follow-up will be 12 months.

# SELECTION OF SUBJECTS

## **Inclusion criteria**

- After receiving information on the design and objectives of the study, the possible risks involved, and the fact that they can refuse to collaborate at any time, patients will give their informed consent to participate in the study and agree to provide material for the cellular and molecular studies.
- Aged over 18 years.
- Chronic HIV infection
- Antiretroviral therapy with at least 3 drugs for at least 2 years and with no modifications expected during the study. Antiretroviral drugs can be switched due to intolerance as long as plasma viremia remains controlled.
- Undetectable viral load determined by ultrasensitive techniques (<50 copies HIV RNA/mL) for at least 2 years.
- CD4+ T lymphocyte count above 350 cells/mm3.
- Demonstration of R5 viral tropism (use of CCR5 coreceptors) or R4/dual tropism (use of CXCR4 or both coreceptors) by phenotyping in plasma samples stored before antiretroviral therapy is started.
- Understand the objective of the study and be available to make frequent visits to the hospital.

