# STATISTICAL ANALYSIS

This is an exploratory pilot study that is trying to prove a concept. Therefore, it is not possible to estimate the size of the sample necessary to demonstrate this. A treatment group of 10 patients has been considered necessary, based on data from previous studies on the same subject, which have used between 4 (Lehrman et al. Lancet 2005) and 11 (Chun et al. J Clin Invest. 2005) patients.

The longitudinal and cross-sectional analysis of the frequency data of infected cells will be carried out using random-effects regression models. In these models, the variable time will be introduced as an independent variable assuming linear kinetics. The frequencies of infected cells will be calculated using a parametric maximum likelihood method described elsewhere for limiting dilution experiments (Myers, L.E., McQuay, L.J. & Hollinger, F.B. Dilution assay statistics. J. Clin. Microb 1994; .32, 732–739) and will be expressed as infectious units per million (IUPM) of resting CD4 T cells. The gradient of the log10 reduction in IUPM will be estimated according to time from the start of therapy. This modelling process will be carried out in 2 approaches. In the first, 2 models will be made to estimate the gradients of log10 reduction in IUPM in the group of patients treated with the drug (n=10). Assuming linear reduction kinetics over time, the half-life will be calculated. The second approach will estimate a single model of the same characteristics as the previous ones but will include an interaction term between time and the treatment received. Given the design of the pilot study (concept), the statistical results will be reported as the estimations together with their standard errors without placing emphasis on the P values found. All the analyses will be carried out using STATA ver 9.0.

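### R5, CXCR4-using and dual-tropic patients are all eligible, but the planned slope analysis for a CCR5 antagonist makes no use of tropism

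*Protocol*

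**What the plan says.** **Eligibility.** The protocol's Inclusion criteria (5.1) ask for "Demonstration of R5 viral tropism (use of CCR5 coreceptors) or R4/dual tropism (use of CXCR4 or both coreceptors", shown by phenotyping of plasma stored before antiretroviral therapy. R5, CXCR4-using and dual virus are all accepted. No number or cap per class is set, and the Exclusion criteria (5.2) do not mention tropism.

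**Hypothesis.** The Rationale states that, if the reservoir is maintained dynamically, "inclusion of CCR5 inhibitors is expected to lead to a reduction in the size of this reservoir". The section on in vivo latency likewise bases the expected influence on adding inhibitors such as CCR5 antagonists. Neither explains why patients whose virus can use CXCR4 are enrolled.

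**Endpoint and analysis.** The primary endpoint is "Size of the latent reservoir measured as the number of resting CD4+ T lymphocytes containing a competent replicating virus". Statistical Analysis (11) says "2 models will be made to estimate the gradients of log10 reduction in IUPM in the group of patients treated with the drug (n=10", without saying what distinguishes the two models. A second approach "will include an interaction term between time and the treatment received". The protocol has no control drug (Synopsis, item 8), and Type of control and design (4.3) is marked not applicable.

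**Data available.** The Study Plan has tropism determined at Baseline 1 for every patient. Statistical Analysis does not name it as a covariate, stratum or subgroup.

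**The concern.** The trial asks whether blocking CCR5 shrinks the reservoir. By the protocol's own gloss, some eligible patients carry virus that can enter through CXCR4, and there is no stated reason to expect the same effect in them. If such patients enter and respond less, the average over the treated group is a blend of two effects, and the blend is closer to background than the effect in R5 patients.

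The cost lies in interpretation. A flat average slope could mean that CCR5 blockade does not reduce the reservoir, or that several patients had virus able to bypass CCR5. The analysis as described has no element that separates these. Its one interaction term concerns treatment received, for which there is no comparison arm.

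**Working it through.** **Is there a planned figure to reproduce?** The sample size of 10 has no calculation behind it. Section 11 says "it is not possible to estimate the size of the sample necessary to demonstrate this" and relies on earlier studies of 4 to 11 patients. No effect size, SD, alpha or power is given. The one related figure that can be checked is the eradication time. With a half-life of 44.2 months and about 10^6 reservoir cells (both in the section on in vivo latency):

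44.2 × log2(10^6) / 12 = 44.2 × 19.93 / 12 = 73.4 years, as the protocol states.

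**Background slope.** b0 = −log10(2)/44.2 = −0.00681 log10 per month, or −0.0817 over 12 months.

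**Dilution.** Let k of the 10 patients be non-R5 and, as the worst case, let them follow background. Then

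all-patient change = (1 − k/10) × b_R5 + (k/10) × b0,

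and the excess over background is (1 − k/10) × (b_R5 − b0). The protocol gives neither k nor b_R5. With an assumed b_R5 of −0.30 log10 at 12 months (excess −0.218):

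| k | All-patient change | Excess over background |
|---|---|---|
| 0 | −0.300 | −0.218 |
| 1 | −0.278 | −0.196 |
| 2 | −0.256 | −0.175 |
| 3 | −0.235 | −0.153 |
| 4 | −0.213 | −0.131 |

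**Range for the R5 effect.** The 12-month all-patient change for k = 0, 2 and 5:
- assumed R5 half-life 6 months: −0.602, −0.498, −0.342
- 12 months: −0.301, −0.257, −0.191
- 24 months: −0.151, −0.137, −0.116

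**Partial response.** If non-R5 patients show a fraction r of the R5 excess, the factor becomes 1 − (k/10)(1 − r). At k = 4 and an assumed r = 0.5 it is 1 − 0.4 × 0.5 = 0.80, against 0.60 at r = 0.

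**Precision of an R5 slope.** With equal per-patient slope variance, its standard error relative to the all-patient slope is √(10/(10 − k)): 1.05, 1.12, 1.20 and 1.29 for k = 1 to 4. At r = 0 the signal-to-SE ratio improves by 1/√(1 − k/10), which is 1.12 at k = 2. At k = 2 the two estimates break even when 1 − 0.2(1 − r) = √0.8 = 0.894, that is r ≈ 0.47. Above that, the all-patient slope is the more informative.

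**Precision of a tropism contrast.** Its standard error relative to the all-patient slope is 10/√(k(10 − k)): 3.3, 2.5, 2.2 and 2.0 for k = 1 to 4. It cannot be estimated at k = 0.

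**The case against.** The strongest reply is that the text shows neither a single pooled slope nor actual dilution. Section 11 speaks of two models and of gradients in the plural. The models are undefined and might be the remnant of a two-group plan, possibly by tropism. The inclusion criterion spells out the added classes, so it looks deliberate, and the stated objectives concern patients on HAART in general, not R5 patients only. An average over those enrolled answers such an objective. The study is also exploratory, reports estimates with standard errors, and has no control, so a null result is ambiguous in any case. A statistical analysis plan that is not shown could add a tropism subgroup.

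Much of this stands, and it rules out several readings a reader might infer:

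- *The primary slope is diluted.* This is not established. It depends on k, which is unknown, and on a lesser response in non-R5 patients. Dual-tropic virus may still enter partly through CCR5, and the phenotype comes from plasma stored before at least 2 years of therapy; no section links it to the virus now in resting cells.
- *The criterion selects nobody.* A stored pre-treatment sample with a demonstrated phenotype is still required.
- *All 10 are certainly pooled into one slope.* The undefined two models leave this open.
- *Non-R5 patients would form an internal negative control.* One to four non-randomised patients cannot carry that weight.

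What the reply does not remove is the mismatch. The hypothesis is specific to CCR5, eligibility is open to virus that does not depend on it, and the protocol links the two nowhere. An analysis plan could add a subgroup but could not supply the reason for the eligibility rule. The protocol has itself named an interaction, and it is not one with tropism.

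**Conclusion.** The point holds as a conditional one. The protocol admits all the tropism classes it names, tests a CCR5-specific mechanism, and describes an analysis that does not use a tropism result it collects. If k is at least 1 and non-R5 patients respond less, the average slope understates the R5 effect, by at most the factor 1 − k/10 on the excess over background. In the example, that moves the 12-month change by 0.02 to 0.09 log10 for k = 1 to 4. The protocol gives no SD against which to judge that shift. At k = 0, or with no drug effect, there is nothing to dilute.

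The bias would be towards background under this assumption, but its size cannot be fixed from the protocol. The firmer consequence is that a null average could not be attributed to the concept rather than to the viral mix. That ambiguity adds to the one from having no control arm, and this part can be reduced without collecting anything new.

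**What to change.** 1. Reconcile the Rationale, the Inclusion criteria and Statistical Analysis by stating why non-R5 patients are admitted and what they are expected to contribute. Who should be eligible is left to the sponsor and investigators.
2. Pre-specify two estimates with standard errors: the on-drug slope of log10 IUPM (Baseline 2 to Month 12) in R5 patients, and the same slope in all patients. Reporting both protects against either assumption about non-R5 response being wrong.
3. If k is at least 1, report the CXCR4-using/dual slope through a time-by-tropism term, descriptively and with its standard error.
4. Let that term replace the between-arm time-by-treatment interaction, which has no control group. If treatment received was meant as on versus off drug, using Months 15 and 18, say so; that term may then stay.
5. Say what the two models are.

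The cost is wording only, since tropism is already determined. The R5 estimate rests on 10 − k patients (standard error about 5% larger at k = 1, 29% at k = 4), and the tropism contrast is imprecise and exploratory only.
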